## **2 Study design**

This is a partially blinded randomized controlled trial with three study groups. Children 6 to 59 months of age presenting at the OPD in Goronyo and diagnosed with one or more of the three study diseases (malaria, diarrhoea and LRTI) are eligible for the study.

Children participating in this study will be randomised to one of 3 study groups to:

- A) Receive 14 days of RUTF supplementation with standard care and treatment or
- B) Receive 14 days MNP supplementation with standard care and treatment or
- C) Be included in a control group receiving standard care and treatment but not receiving nutritional supplementation (control group)

Individual follow-up will be 6 months. During this time, children in the RUTF or MNP group will receive 14 days nutritional supplement every time diagnosed with at least one of the three study diseases, not exceeding more than 14 days supplementation in any 28 day period.

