### **3 Endpoints**

#### **3.1 Primary endpoint**

The primary endpoint is “negative nutritional outcome (NNO)” of a child within the 6 months follow-up period. The incidence of a negative nutritional outcome will be defined in two different ways according to the baseline nutritional status:

- for children with no malnourishment at time of entry into study, “negative nutritional outcome” is defined as progression to moderate or severe malnourishment,
- for children with moderate malnourishment at time of entry into study, “negative nutritional outcome” is defined as loss of  $\geq 10\%$  of baseline weight or progression to severe malnourishment, whichever is reached first.

Thus, the event of a child reaching a “negative nutritional outcome” at least once within 6 months of follow-up period will be compared between the three study groups.

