#### **3.2 Secondary endpoints**

Secondary endpoints include

- Number of NNO’s per study group in a period of 6 months
- Time to NNO
- Number of new events of a study disease in 6 months
- Weight change at 14 days and 28 days after study inclusion, and at end of study period
- Rate of weight change (grams/kg/day) at 14 days and 28 days after study inclusion, and at end of study period
- Proportion of children not gaining weight (including losing weight), measured at day-14 and day-28 after study inclusion.
- Proportion of children developing bilateral oedema, overall and per month
- Proportion of moderate acutely malnourished children improving to a non acutely malnourished state, overall and per month
- Mortality: overall mortality
- Morbidity, including the three study diseases (proportion of children with newly diagnosed diseases), overall and per month
- Proportion of children with a reported cough at clinical visit, overall and per month
- Proportion appetite categories
- Proportion and time pattern of children who were breast-fed at baseline and stopped being breast-fed during the study

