#### 5.4.3 Subgroups

Stratified analysis will be done for three pair-wise comparisons (RUTF vs. control, MNP vs. control, RUTF vs. MNP (as described in 5.4.1) according to the following subgroups (measured at baseline):

- age (binary: <36 months, ≥36 months)
- gender
- current breastfeeding practices (no, partial breast feeding)
- underlying illnesses (only malaria, only diarrhoea, only LRTI, 2 or more diseases)
- socio-economic status (low, moderate, high)
- food availability (binary or in tertile)
- length of illness before visiting MSF clinic (binary or in tertile)
- recruitment period (binary or in tertile)
- malnourishment status(non-acutely malnourished or moderately acutely malnourished)

To assess the presence of effect modification for these factors, models with interaction terms will be analysed.

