## **5.5 Analysis of secondary endpoints**

All secondary endpoints (as defined in section 3.2) will be compared between the three treatment groups as described in 5.4.1 (p-values will be considered explorative) for the ITT and the PP populations. In addition to the Poisson regression model, logistic regression model, analysis of variance (ANOVA), analysis of covariance (ANCOVA), Cox proportional hazard model, and non-parametric analysis of variance will be used, according to the type of endpoint. In case of relevant differences in baseline characteristics additional adjustment(s) for these factors may be performed. Stratified analyses are planned for secondary endpoints regarding weight and weight change with respect to age, gender, and breast feeding.

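### Section 5.5 leaves diarrhoea at entry out of the day-14 and day-28 weight analyses, which costs precision without biasing the randomised comparison

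*SAP*

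**What the plan says.** Section 2 of the SAP takes in children 6 to 59 months old who are "diagnosed with one or more of the three study diseases (malaria, diarrhoea and LRTI) are eligible for the study". Weight at inclusion is therefore a weight during acute illness.

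Section 3.2 runs three weight endpoints from inclusion. Two are continuous: the total change and its rate in g/kg/day, each taken at day 14, day 28 and the close of follow-up. The third is binary: "Proportion of children not gaining weight (including losing weight), measured at day-14 and day-28 after study inclusion".

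Section 5.5 compares the secondary endpoints as in 5.4.1, where the only named covariate is nutritional status at enrolment. It then adds: "Stratified analyses are planned for secondary endpoints regarding weight and weight change with respect to age, gender, and breast feeding". Further adjustment is permitted, not required, and only where baseline characteristics differ to a relevant degree.

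Section 5.4.3 lists a subgroup factor "underlying illnesses (only malaria, only diarrhoea, only LRTI, 2 or more diseases" with interaction models, but as part of the secondary analysis of the primary endpoint. Section 5.5 refers back to 5.4.1 and does not carry 5.4.3 over.

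**The concern.** A child weighed while short of fluid will show a gain once the fluid returns, whichever arm the child is in. In such a child, change from inclusion mixes tissue change with rehydration. Diarrhoea at entry is then a strong predictor of short-term weight change, and one that randomisation will usually balance. An adjustment clause triggered by imbalance will therefore seldom reach it.

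The SAP recognises entry illness as worth separating for the primary endpoint. It leaves it out where short-term fluid regain would act most directly, over the first 14 and 28 days. These comparisons are named secondary objectives in section 1.2, and data up to day 28 also feed Pooled analysis I (section 5.7.1). What is at stake is how precisely mean change is estimated, and how large the absolute difference in failure to gain looks. If the share with diarrhoea differs between sites, that absolute difference could vary across the pooled studies for this reason alone.

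**Working it through.** The SAP gives no sample size, SD, weight effect, share with diarrhoea or hydration data, so there is no figure of its own to reproduce. Every input below is an assumption.

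**Inputs.** Tissue change as % of weight is Normal with mean 1% (control) or 2% (supplement) and SD s = 2.5 or 3.5. A fraction f = 0.2, 0.4 or 0.6 has diarrhoea at entry. These children regain a fluid deficit with mean d = 3% or 5% and SD 1.5%, the same in each arm. That makes 12 scenarios.

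**Scale.** A 5% deficit in an 8 kg child is 400 g. From the entry weight of 7.6 kg, fluid alone gives 400 / 7.6 / 14 = 3.8 g/kg/day over 14 days.

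**Mean difference.** Each arm's mean rises by f × d, so the difference stays (2 + f·d) − (1 + f·d) = 1 point. There is no bias.

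**Variance of weight change.**
- Diarrhoea ignored: V = s² + f·1.5² + f(1−f)·d²
- Diarrhoea as a model term: V = s² + f·1.5²

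| Scenario | Ignored, relative to s² | With term |
|---|---|---|
| Smallest (s 3.5, f 0.2, d 3) | (12.25 + 0.45 + 1.44) / 12.25 = 1.15 | 12.70 / 12.25 = 1.04 |
| Largest (s 2.5, f 0.6, d 5) | (6.25 + 1.35 + 6.00) / 6.25 = 2.18 | 7.60 / 6.25 = 1.22 |
| Milder (s 2.5, f 0.4, d 1) | (6.25 + 0.90 + 0.24) / 6.25 = 1.18 | 7.15 / 6.25 = 1.14 |

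Over the 12 scenarios, inflation of 15–118% falls to 4–22% with the term. In the milder case, which lies outside the 12, the term recovers little.

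**Failure to gain.** P(change ≤ 0) = Φ(−mean / SD), where SD = √(s² + 1.5²) in children with diarrhoea.

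| | s = 2.5 | s = 3.5 |
|---|---|---|
| No diarrhoea: control, supplement | 34.5%, 21.2% | 38.8%, 28.4% |
| Difference; risk ratio | 13.3 points; 0.61 | 10.4 points; 0.73 |
| Diarrhoea, d = 3: control, supplement (difference) | 8.5%, 4.3% (4.2) | 14.7%, 9.5% (5.2) |
| Diarrhoea, d = 5: control, supplement (difference) | 2.0%, 0.8% (1.2) | 5.8%, 3.3% (2.5) |
| Pooled difference, f = 0.4, d = 3 or 5 | 9.6 or 8.4 | 8.3 or 7.2 |
| Pooled risk ratio, all f and d | 0.59–0.61 | 0.70–0.73 |

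For example, at s = 2.5, f = 0.4 and d = 3, the pooled difference is 0.6 × 13.3 + 0.4 × 4.2 = 9.6 points. The absolute difference shrinks. The risk ratio hardly moves, because most events come from children without diarrhoea.

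**Second illustration, in grams.** Assume a control gain of 100 g, an effect of 100 g, SD 300 g, 142 per arm (80% power with no fluid regain), 20–50% with diarrhoea, and a mean regain of 200–500 g with SD half the mean. Ignoring diarrhoea lowers power for mean change to 77–50%; a diarrhoea term brings it to 79–68%. The difference in failure to gain falls from 11.7 points to 10.7–7.1, while the risk ratio goes from 0.68 to 0.66–0.68.

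**Would restricting to children without diarrhoea help?** The variance per enrolled child becomes s² / (1−f), a factor of 1.25, 1.67 or 2.50. At each f this is worse than the model term, whose largest factors are 1.07, 1.14 and 1.22. Even the unadjusted all-children analysis is more precise for mean change in 8 of the 12 scenarios. For failure to gain, its test statistic is at least as large in 9 of 12 (one of them a tie to within 0.2%), and only 2–3% smaller in the other three.

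**The case against.** The strongest reply is that nothing in section 5.5 is misstated. Age, gender and breast feeding are a legitimate choice of strata, the endpoints are secondary with explorative p-values, ANCOVA is among the named methods, and nothing forbids a supportive breakdown by entry illness. The size is also assumed. The SAP recruits outpatients, and section 4.2 lists hospitalisation for serious complicated illness as an exclusion criterion, so many deficits may be mild. The weighing procedure may stand in the protocol, which is not shown. All of this is fair. It makes the point a modest one about precision. It does not explain why a predictor used for the primary endpoint is dropped for short-term weight, and an optional clause triggered by imbalance does not cover a balanced predictor.

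A reader might go further and infer that fluid regain hides the supplement effect, or that the failure-to-gain endpoint tells us almost nothing in children with diarrhoea. The documents do not support either. The mean difference is unbiased and the pooled risk ratio is nearly unchanged. At s = 3.5 and d = 3, about 15% of controls with diarrhoea still fail to gain.

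A reader might also infer that the endpoint "Proportion of moderate acutely malnourished children improving to a non acutely malnourished state, overall and per month" counts children who were moderately malnourished only while dehydrated. The SAP does not say how that status is measured or what the children's hydration was, so this is conjecture.

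**Conclusion.** The point holds as a matter of precision and presentation. Section 5.5 omits a likely strong predictor of day-14 and day-28 weight change, although the SAP already uses entry illness elsewhere. Under the stated assumptions, ignoring it inflates the variance of weight change by about 15–118%, and a model term cuts this to 4–22%. The absolute difference in failure to gain falls from 13.3 to 8.4–9.6 points (s = 2.5), or from 10.4 to 7.2–8.3 points (s = 3.5), at 40% diarrhoea.

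All of this rests on fluid regain after entry, which is an inference. With a 1% deficit at 40% diarrhoea and s = 2.5, the variance rises 18% and the pooled difference is 11.7 points. The validity of the randomised comparison of measured weight is not in question. It would be wrong to conclude that inference should move to children without diarrhoea: that generally loses precision, and it departs from the section 1.2 objectives, which are not limited to such children.

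**What to change.** In section 5.5, before unblinding:

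1. Name diarrhoea at enrolment (yes/no) as a fixed term in the day-14 and day-28 models for weight change, g/kg/day and failure to gain, whatever the observed baseline balance. A yes/no indicator is needed because the category for two or more diseases in 5.4.3 mixes children with and without diarrhoea.
2. Add the same indicator to the planned stratified analyses of the weight endpoints, as a supportive table.
3. State that the analysis of all enrolled children remains the main one.

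For failure to gain, show the absolute risks by arm beside any model-based ratio, so that the smaller absolute difference can be read in context.

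The cost is a short text change and one more explorative table per weight endpoint, with wider intervals within strata. The variable comes from entry diagnoses already needed for 5.4.3.

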## **5.6 Analysis of safety measures**

The proportion of children with serious adverse events or serious adverse reactions will be presented by frequencies and percentages for each treatment group. The number of serious adverse events and serious adverse reactions will be presented by frequencies for each treatment group.

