#### **3.3 Safety measures**

- Serious adverse events
- Serious adverse reactions

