# **5 Statistical analysis**

## **5.1 Analysis of baseline data**

All available data at baseline will be analysed descriptively for each intervention group and in total. Results will be summarised as frequencies and percentages for nominal data; as means, standard deviations, and range for continuous data; and as medians, quartiles, and ranges for ordinal data.

Differences regarding baseline variables will be checked for clinical relevance between the three treatment groups.

The flow of participants will be described (e.g. number screened, recruited, randomized, emergency unblinding, etc.). Number and reasons for drop-out, lost-to-follow-up, or withdrawal will be presented. If possible respondents and non-respondent will be compared.

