### 5.3 Primary analysis of primary endpoint

The primary endpoint is “negative nutritional outcome” of a child within the 6 months follow-up period. The incidence rate (in formulae below referred to simply as ‘rate’) of “negative nutritional outcome” will be computed as the number of events divided by total observed person-time in each treatment group. As an “event” the first time a child reaches a negative nutritional outcome will be used. The primary analysis of the primary endpoint will be performed on the intention to treat population with no imputation of missing data.

In the primary analysis, RUTF will be compared to the control group

The hypotheses in this step are

$$H_0: \text{rate}_{\text{RUTF}} = \text{rate}_{\text{Control}}$$

vs.

$$H_1: \text{rate}_{\text{RUTF}} \neq \text{rate}_{\text{Control}}$$

where  $\text{rate}_{\text{RUTF}}$  = rate of “negative nutritional outcome” in the children in the RUTF group, and  $\text{rate}_{\text{Control}}$  = rate of “negative nutritional outcome” in the children in the control group.

The comparison of rates among the two treatment groups (RUTF vs. control) will be performed by a Poisson regression model, adjusted for nutritional status at enrolment (fixed effect) and will be performed within one model including the three intervention groups with contrasts for each two-group comparison. The result will be presented as rates for each intervention group, and a rate ratio for the pair-wise comparison (each with 95% confidence intervals). Tests will be two-sided with a significance level of 0.05.

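### The SAE summary in 5.6 gives crude counts and percentages only; adding observation time and a rate ratio with an interval would show what size of harm is excluded (minor)

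*SAP*

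**What the plan says.** SAP 3.3 lists two safety measures, headed by "Serious adverse events", apart from the secondary endpoints of 3.2. SAP 5.6 handles them in two sentences. At child level: "The proportion of children with serious adverse events or serious adverse reactions will be presented by frequencies and percentages for each treatment group". At event level: "The number of serious adverse events and serious adverse reactions will be presented by frequencies for each treatment group". Nothing else in the SAP analyses them, because 5.5 confines its between-group comparisons to the endpoints of 3.2. Overall mortality is among those, so fatal events do get a comparison. Non-fatal SAEs and all serious adverse reactions do not.

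The primary endpoint is treated differently. In 5.3 its incidence rate "will be computed as the number of events divided by total observed person-time in each treatment group", and the result is a rate per group and a rate ratio, each with a 95% confidence interval.

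On follow-up, section 2 states: "Individual follow-up will be 6 months". Section 5.1 expects some children to be lost: "Number and reasons for drop-out, lost-to-follow-up, or withdrawal will be presented". The SAP gives no expected loss rate and no expected SAE rate.

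**The concern.** A count of events, or the share of an arm's children with an event, depends on how long the children were watched as well as on their risk. An arm that loses more children, or loses them sooner, shows fewer SAEs at the same true rate. The SAP allows for unequal observation in its efficacy analysis and makes no such provision for safety. The event count in 5.6 has no denominator at all.

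The second limb does not depend on unequal loss. SAEs may be few. Two small counts side by side, with no estimate and no interval, invite the reading that the arms do not differ, even when a substantial excess is compatible with the data. What is at stake is how well the trial can describe the safety of the two supplements; the primary efficacy conclusion is not touched.

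**Working it through.** The SAP states no figure on this point, so there is nothing to reproduce. The following is an illustration.

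**Inputs from the SAP.** Six months of follow-up per child (section 2); crude counts and percentages for SAEs (5.6); person-time and a rate ratio with 95% CI for the primary endpoint (5.3).

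**Assumed inputs.** A constant SAE rate, equal in both arms, of 0.02, 0.05 or 0.10 per child per 6 months. Losses of 5% vs 10%, 5% vs 20% and 10% vs 30%, unrelated to SAE risk, either spread evenly over 6 months or all at month 1. Percentages are taken over all children in the arm.

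**Step 1: event counts.** Expected events per child = rate × mean share of the 6 months observed. With loss d, that share is 1 − d/2 for even loss and 1 − d + d/6 for loss at month 1. At equal rates, the ratio of counts is the ratio of these shares.

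| Loss | Timing | Mean share observed | Count ratio, arm with more loss / other arm | True rate ratio that would appear as equal counts |
|---|---|---|---|---|
| 5% vs 10% | even | 0.975 vs 0.950 | 0.974 | 1.026 |
| 5% vs 10% | month 1 | 0.958 vs 0.917 | 0.957 | 1.045 |
| 5% vs 20% | even | 0.975 vs 0.900 | 0.923 | 1.083 |
| 5% vs 20% | month 1 | 0.958 vs 0.833 | 0.870 | 1.150 |
| 10% vs 30% | even | 0.950 vs 0.850 | 0.895 | 1.118 |
| 10% vs 30% | month 1 | 0.917 vs 0.750 | 0.818 | 1.222 |

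The distortion runs from about 3% to 18%. With equal losses and equal timing the ratio is 1. Dividing by person-time returns 1.00 in every row.

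**Step 2: percentages of children.** Crude percentage = (1 − d)(1 − exp(−rate)) + d × P(event before loss). Example: rate 0.05, 5% vs 20% lost at month 1.
- 0.95 × 0.04877 + 0.05 × 0.00830 = 4.67%
- 0.80 × 0.04877 + 0.20 × 0.00830 = 4.07%
- Ratio 0.87, as for counts.

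Over all three assumed rates, the percentage ratios agree with the count ratios to within 0.002.

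**Step 3: what if the lost children are at higher risk?** Let 20% of each arm be frail, with k times the rate of the others. Only frail children are lost, all at month 1, 5% vs 20%. Relative to the non-frail rate, events per child = 0.8 + (0.2 − d)k + dk/6.
- k = 2: 0.867 / 1.117 = 0.78 for counts. Dividing by 0.833 and 0.958 of the period gives 1.040 / 1.165 = 0.89 for rates.
- k = 3: 0.900 / 1.275 = 0.71 for counts, and 1.080 / 1.330 = 0.81 for rates.

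Person-time then removes only part of the distortion.

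**Step 4: the missing interval.** Take 16 vs 8 first events over equal person-time (assumed counts). Rate ratio = 2.0. SE of its log = √(1/16 + 1/8) = 0.433. 95% CI = exp(0.693 ± 1.96 × 0.433) = 0.86 to 4.67. Exact limits are 0.81 to 5.40. The planned table would show the two counts and neither interval.

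**The case against.** The case for leaving 5.6 alone has weight. Descriptive SAE tables are common, the section states nothing false, and person-time for the primary endpoint does not oblige the SAP to use it in every table. Drop-out and its reasons are reported by 5.1, so unequal loss would be visible. The distortion is small beside the sampling error: at 5% vs 10% loss it is 3% to 4%, against the wide interval in the 16 vs 8 example. A reader could also compute a crude interval from the percentages of children.

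Most of this stands, and it is why the point is minor. It does not remove the point. A reader's own interval would rest on the crude percentages and could not allow for observation time, and the event counts carry no denominator from which to build one.

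Several stronger readings are tempting and are not supported:

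- **Control children will be lost more often because they receive no product.** The SAP gives no loss rates, sets the same 6 months for every child and describes standard care in all three groups. If control did lose more, the supplements would look worse than they are, so harm would be exaggerated rather than hidden.
- **The safety conclusion rests on this table alone.** Overall mortality is compared between arms under 5.5, although the SAP does not say which model applies to it.
- **Person-time would correct the bias.** It does so only if loss is unrelated to SAE risk and the rate is roughly constant over time; step 3 of the working shows what remains otherwise.
- **The person-time of 5.3 can be reused.** There the event is the first negative nutritional outcome, and the SAP does not say whether observation time continues after it.

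**Conclusion.** The concern holds as a minor weakness. Section 5.6 gives no observation time, between-arm estimate or interval for SAEs, and no other section supplies them, apart from the partial overlap with mortality.

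The distortion from unequal follow-up is conditional and modest: about 3% to 18% relative under the assumed losses, none if losses and their timing are equal. It rests on assumed loss patterns, a constant SAE rate and loss unrelated to risk. The SAP neither predicts nor rules out such losses. The lack of an interval holds whatever the losses are.

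A reader might infer that the planned table is wrong or that the trial's safety conclusion will be biased. The document supports neither. The table is usable but incomplete, and a better summary is cheap.

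**What to change.** Keep the planned counts and percentages. Add to 5.6:

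1. For each arm, child-months of observation for safety. For the analysis of children with an SAE, time runs to the first SAE or the end of observation, whichever comes first. For event counts, it runs to the end of observation. Derive both separately from the person-time of 5.3, which may end at the first negative nutritional outcome.
2. For each arm, the rate of first SAEs per child-month, and the rate of all SAEs including repeats.
3. Descriptive rate ratios for first SAEs, RUTF vs control and MNP vs control, with exact 95% confidence limits. No hypothesis test is needed. Report repeat events as rates per arm only, which avoids having to model correlation within a child from few events.
4. Serious adverse reactions remain descriptive, because control receives no product and so offers no natural comparator for product reactions.
5. One sentence stating that person-time reduces bias from unequal loss only as far as loss is unrelated to SAE risk, with a cross-reference to the drop-out summary of 5.1.

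Cost: SAP wording, a small extra derivation and one more table. No change to the design is needed. The downside is that the intervals will be wide if events are few.
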